## Statistical method

We will perform mainly between-subject analysis by comparing the mean outcomes of the experimental group with the mean outcomes of the control group. To analyze the clinical outcomes related to disability and impairment, we will calculate the normalized improvement, which shows improvement or decline in proportion to the maximum score possible in the respective scale, therefore avoiding ceiling effects. Depending on whether the data is following a normal distribution, we will use parametric or non-parametric statistics. In the case of non-normal data, medians will be reported. We will perform an intention-to-treat analysis. The last observation carried forward analysis will be performed alongside a complete-case analysis to account for missing data.

To address the *primary outcome on disability and impairment*, a between-subject analysis will be used to compare the change in disability (Barthel Index (BI)) between the experimental and control groups at baselines 3, 6, and 12 months.

For the *secondary outcomes* on usability and impairment and other planned comparisons, we will perform the following analysis (for abbreviations, see Table 2):

Changes in independence (CAHAI), participation (SIS), depression (HDRS) fatigue (FSS), pain (VAS), spasticity (mAS), and impairment (BI and FM-UE) are analyzed from baseline to months 3 and 12.

We will also look at the change in grip force and correlate it with FM-UE, CAHAI, and BI from baseline to 3 months and 12 months. The outcomes of this measure are important to evaluate the clinical effectiveness of the RGS intervention to reduce disability and impairment. To measure quality of life, we compare the group changes in the quality of life (SSQOL) and well-being (SF-36) from baseline to 3 months and 12 months. We will also compare well-being (SF-36) at 6 months.

For the additional variables shown in Table 3, we will proceed as follows:

*Readmission*: We compare between the groups the number of outpatients that return to the hospital after discharge to at-home status, including readmission due to complications unrelated to stroke, from baseline to 3, 6, and 12 months. We also compare the days of hospitalization and their associated costs. Here, we will take into account the presence of CVA risk markers as covarying variables. The readmission outcome is used to evaluate the effectiveness of the RGS intervention in reducing, or at least not increasing, a hospital’s readmission after discharge compared to standard care.

*Cost of treatment*: We compare the total cost of rehabilitation therapy/hour provided at the hospital or in the community and transportation costs/hour between the hospital and home at 3 months and after 12 months. We also compare days/hours of hospitalization and whether additional therapy, not replacing the RGS-based training (e.g., magnetotherapy, electrotherapy, thermotherapy), was provided. These outcomes allow us to evaluate the RGS’s effectiveness to reduce the cost of treatment.

*Quality of life*: We will compare between the groups the number of falls reported at 3 months and 12 months. In addition, we will compare how many patients were able to return to work and how many hours professional care was provided at 3 and 12 months. These outcomes facilitate the evaluation of the impact of the RGS ecosystem on quality of life and evaluate any risks arising from using the RGS system at home.

*Acceptance*: We will assess the RGS@home use (hours) after 3 months, 6 months, and 12 months. In both groups, we will keep track of the dropouts of the study. Specifically, in the intervention group, we will analyze the use of RGS at the hospital and home and the use of RGSwear. Concerning RGS@home, we will analyze the support needed (hours and visits to the patient’s home, replacement of materials, instructions, troubleshooting, etc.) and any incidents reported by the users. Also, we will analyze the patient’s evaluation of the System Usability Scale. The outcomes of this domain are important to evaluate the acceptance of the RGS ecosystem within the experimental group and the feasibility of the system for future use.

Lastly, we will analyze the kinematic data obtained from the motion tracking devices and the RGS training exercises. We will estimate the change in clinical scales from changes in kinematics and performance according to a data analysis regression pipeline that we have previously developed [17].

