**Inclusion criteria**	
Patients presenting a first-ever ischemic or intracerebral hemorrhagic stroke	
A CT scan and/or MRI to exclude other pathologies	
Lesion localization by clinical symptoms/signs	
Moderate to mild proximal upper limb motor impairment (MRC ≥ 2) and/or moderate to severe non-fluent aphasia (Barcelona test or equivalent)	
Age 20–85 years old	
Able to sit on a chair or a wheelchair interacting with RGS during a full session and be capable and willing to participate in RGS therapy	

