#### Primary outcome measures

One main outcome measure is calculated as a compound score summarizing the main outcome of each of the 5 domains: (1) disability and impairment (Barthel Index for independence in activities of daily living), (2) readmission (number of patients who return to the hospital (inpatient) after being discharged to at-home status), (3) cost of treatment (total cost of the therapy), (4) quality of life (the Stroke Specific Quality of Life Scale), and (5) acceptability (amount of use at home).

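### Dividing Barthel change by the scale maximum does not avoid ceiling effects as the plan states; the claim should go and the raw follow-up score be compared with baseline as covariate.

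*Protocol article*

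**What the plan says.** Under Statistical method, the protocol article sets one derived variable for a whole domain: "To analyze the clinical outcomes related to disability and impairment, we will calculate the normalized improvement", described as a quantity "which shows improvement or decline in proportion to the maximum score possible in the respective scale, therefore avoiding ceiling effects". No formula is printed. The same section then names the primary disability comparison: "a between-subject analysis will be used to compare the change in disability (Barthel Index (BI)) between the experimental and control groups", at 3, 6 and 12 months. The choice of test is left to the data: "Depending on whether the data is following a normal distribution, we will use parametric or non-parametric statistics". It also commits to an intention-to-treat analysis.

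Under Primary outcome measures the Barthel Index is one of five parts: "One main outcome measure is calculated as a compound score summarizing the main outcome of each of the 5 domains". Eligibility (Table 1) reaches down to mild arm impairment and also admits patients on language grounds: "Moderate to mild proximal upper limb motor impairment (MRC ≥ 2) and/or moderate to severe non-fluent aphasia (Barcelona test or equivalent". Table 1 sets no upper limit on the baseline Barthel score.

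**The concern.** A ceiling effect means that patients near the top of a scale cannot register further gain. Dividing every patient's change by the same number cannot create room at the top. The section names no other measure against a ceiling, so a reader would take the matter as settled.

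This matters because Barthel change is the only comparison that the statistical section labels primary, and the trial is small: 90 patients, 60 against 30, a number set by feasibility. With mild impairment admitted and chronic outpatients included, some patients may start near the top. If the Barthel shows no difference, the text as it stands would let a reader rule out the ceiling as an explanation when it has not been ruled out.

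**Working it through.** **Inputs from the protocol article:** 60 intervention and 30 control patients (three hospitals × 20 + 10); between-group comparison of Barthel change; parametric or non-parametric test. The article states no alpha, power, effect size or SD, so there is no figure of its own to reproduce.

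**Literal reading.** Let B be baseline, Y follow-up and M the scale maximum. Normalized improvement = (Y − B)/M. With M the same for everyone, the difference in means is multiplied by 1/M and so is its standard error, so the t statistic is unchanged. Ranks are unchanged too, so the Mann-Whitney test is unchanged. A patient starting at 95 of 100 can still gain at most 5 points, or 5/100 = 5%.

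**Alternative reading.** (Y − B)/(M − B), the share of the possible gain. Three consequences:
- At B = M the denominator is 0 and the value is undefined.
- Gains stop at +100%, but a fall from 95 to 85 gives (85 − 95)/(100 − 95) = −10/5 = −200%.
- The divisor now differs between patients, so the test does change.

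**Simulation of both readings.** All of these are assumptions: scale 0–100 in steps of 5, baseline SD 20, control gain 10, true extra gain 8, SD of change 12, two-sided 0.05, 60 against 30, 3,000 trials per row.

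| Assumed baseline mean | At maximum at baseline | At maximum at follow-up | Observed extra gain | t-test power, uncapped scale | raw change | change/M | change/(M − B) |
|---|---|---|---|---|---|---|---|
| 50 | 0.9% | 8.6% | 7.47 | 83.3% | 79.5% | 79.5% | 67.4% |
| 65 | 5.2% | 23.5% | 6.53 | 83.9% | 71.7% | 71.7% | 64.9% |
| 75 | 13.0% | 38.2% | 5.44 | 84.1% | 59.7% | 59.7% | 59.9% |
| 85 | 26.8% | 54.9% | 4.17 | 83.9% | 43.0% | 43.0% | 52.9% |

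P-values for raw change and change/M differed by at most 2 × 10⁻¹⁵, which is rounding, for both the t-test and Mann-Whitney. The share of the 8 points lost to the cap runs from (8 − 7.47)/8 = 7% to (8 − 4.17)/8 = 48%. Change/(M − B) loses power at low baselines, is level at 75 and gains about 10 points at 85. It can be computed only after dropping the patients in the second column.

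**What baseline adjustment does and does not do.** Assume a mix of inpatients (baseline mean 55) and outpatients (88), latent effect 7, 60 against 30.
- Effect size: with control gains of 20 and 3 points and change SD 12, the estimated effect at inpatient shares 0.3/0.5/0.7 is 4.81/5.04/5.45 for raw change and 4.83/5.08/5.43 with baseline as covariate. The compression is the same.
- Precision: for the same two-group mix, in a separate run of 2,000 trials per inpatient share, power was 43/40/43% for change and 66/60/57% adjusted, a gain of 23/20/14 points. With equal gains in the two groups the advantage is about 5–9 points. With a single baseline mean of 65 it is about 1–2 points (66–68% against 68–70%).

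**The case against.** The fairest defence is that this is one loose phrase in a condensed article. The exact formula may stand in the full protocol, and the phrase may be shorthand for gain relative to possible gain. That reading does act on the ceiling: in the scenario with baseline mean 85 it lifts power from 43.0% to 52.9%. This stands, so it would be wrong to say the normalization does nothing on every reading. It does not rescue the sentence, because the article itself draws the conclusion that ceilings are avoided, and partial easing with undefined values for some randomised patients is not avoidance.

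A reader might also infer more than the documents support:
- *That the primary comparison is invalid or biased.* On the literal reading it is the ordinary change-score test, a valid randomised comparison. No bias between arms or inflation of type I error follows.
- *That the Barthel is the only primary component with an efficacy test.* The statistical section also sets between-group comparisons for stroke-specific quality of life, readmission and cost. The Barthel is only the one labelled primary there.
- *That baseline adjustment would recover the effect lost at the top.* It would not, as the estimates above show. Its benefit is precision.
- *That the rule breaks down for depression, pain, fatigue and spasticity because a high score is bad there.* Under a fixed divisor only the sign changes. Grip force is dealt with in a separate sentence.
- *That a severe ceiling is known to exist.* Eligibility limits arm strength or aphasia, not the Barthel.

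**Conclusion.** The point holds in limited form. The stated property is wrong on either reading: a fixed divisor leaves the tests and the ceiling exactly as they were, and division by the remaining room is undefined at the maximum and lopsided. The first half is algebra and needs no assumption beyond the literal wording.

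The practical size is not known. The 7–48% loss of effect and the power gain of about 1–2 to about 20 points both rest on assumed Barthel distributions, including a 0–100 scale. Severity is moderate: the planned test is inefficient and its interpretation is put on a false footing, but it is not biased between arms.

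**What to change.** In Statistical method:
1. Delete the statement that the normalization avoids ceiling effects.
2. For the Barthel and the other scales, compare the raw follow-up score between arms with the baseline score of the same scale as covariate. Keep normalized values for description only, with the formula printed.
3. Report the percentage of patients at the maximum score by arm at baseline and each visit, so that a null result can be interpreted.
4. Optionally, add a supportive ordinal or Tobit model for the Barthel, since baseline adjustment does not address the ceiling.

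The cost is the rewording of one paragraph; Table 2 already schedules the scales at baseline. The one small loss is that results no longer share a single percentage scale across instruments.

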### Allocation and blinding

After being assessed for eligibility, patients are randomly allocated to either the intervention or control group (allocation ratio 2:1). The larger sample size in the experimental group allows more variables to be tested and gives more power to detect relevant effects in the experimental intervention. Randomization is realized via an adaptive stratified sampling (i.e., minimization) through the computerized encrypted cloud-based database (electronic case report form (eCRF)), which takes into account three conditions to balance the two groups: (1) time since stroke (≥ 30 days), (2) age (≥ 20 years old), and (3) severity (≥ 2 MRC). The allocation is concealed while patients and clinicians (except those involved in the baseline assessment) are not blind to the group allocation. A sham group was excluded from the design because an earlier study has shown a superior rehabilitation effect of training with RGS over sham computer game training using the Wii gaming console [10]. Since this is a first-of-a-kind study evaluating the outcomes (see Tables 2 and 3.) of an AI platform for rehabilitation, the sample size has been determined by feasibility (3 years) and estimated by considering the monthly number of eligible inpatients and outpatients of the participating hospitals. We plan to include a total of 90 patients via the clinical partners in the consortium. Each hospital will be recruiting 30 patients, 20 in the intervention group and 10 in the control group.

**Table 2 Tab2:** Study procedure and assessment

Study procedure	Screening and baseline assessment		Control group, standard care	Intervention group, 0–3 months daily sessions of 24 min or more	Post-treatment assessment		
	Inpatients	Outpatients			3 months	6 months	12 months
Informed consent	x	x					
Medical history	Patients’ demographics MRI/CT scan when available						
Assessment: domains and scales							
Disability and impairment	Barthel Index (BI)				x	x	x
	Stroke Impact Scale (SIS)				x		x
	Fugl-Meyer Assessment of the upper limb (UE-FM)				x	x	x
	Chedoke Arm and Hand Activity Inventory (CAHAI)				x		x
	Hamilton Depression Rating Scale (HDRS)				x		x
	Visual analog score (VAS) for pain				x		x^a^
	Modified Ashworth Scale (AS) for spasticity				x^a^		x
	Fatigue Severity Scale (FSS)				x		x
	Grip force^a^				x^a^		x^a^
	Kinematics from the motion capture camera of the RGS@home system				x	x	x
	RGSwear data (paretic arm)				Continuous		
	Incidents related to use				x		x

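### Dividing change by the scale maximum does not avoid ceiling effects, and comparing change scores is less precise than adjusting for the baseline score already collected

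*Protocol article*

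**What the plan says.** All of this is in the Protocol article, section Statistical method, unless noted.

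- Disability and impairment outcomes are to be expressed as a normalised improvement, that is, "improvement or decline in proportion to the maximum score possible in the respective scale, therefore avoiding ceiling effects". No formula is given.
- The general approach is a between-subject analysis, "comparing the mean outcomes of the experimental group with the mean outcomes of the control group". For the Barthel Index this is made specific: "a between-subject analysis will be used to compare the change in disability (Barthel Index (BI)) between the experimental and control groups". The other scales are likewise analysed as change from baseline.
- The test family depends on the data: "Depending on whether the data is following a normal distribution, we will use parametric or non-parametric statistics". Medians are reported when normality fails.
- Covariates are named only for readmission: "we will take into account the presence of CVA risk markers as covarying variables".
- Sample size (section Allocation and blinding): "We plan to include a total of 90 patients via the clinical partners in the consortium". It rests on feasibility, and no SD, effect size, correlation or power is stated. Minimisation uses time since stroke, age and severity.

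**The concern.** The plan tells readers that a known bias has been dealt with when it has not. Table 1 admits patients with mild upper-limb impairment, and aphasia alone can also qualify a patient. Some patients may therefore start near the top of the Barthel Index or the upper-limb Fugl-Meyer. If so, a true benefit is compressed, and nothing in the stated index corrects this.

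The second issue is efficiency. With recruitment fixed by feasibility and only 30 controls planned, the analysis is one of the few places where precision can still be gained. A change score uses the baseline with a fixed coefficient of 1. A regression estimates that coefficient from the data and is at least as precise in large samples.

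**Working it through.** **Sample size.** "Each hospital will be recruiting 30 patients, 20 in the intervention group and 10 in the control group" gives 3 × 20 = 60 and 3 × 10 = 30, total 90, which agrees with the stated total and the 2:1 ratio. There is no power figure to reproduce.

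**Step 1: literal reading of the index.** Let D be a patient's change and M the scale maximum, the same for everyone. For D/M, the difference in means and its standard error are both divided by M, so the t statistic is unchanged. Ranks are unchanged because M is positive. No assumed figure is needed. In simulation, the t-test p-values for raw and normalised change were identical in every trial.

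**Step 2: remaining-room reading.** Take D/(M − baseline), with M = 100 assumed for the Barthel Index (the article does not give its range).

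- From 95 to 90: −5/(100 − 95) = −1.0.
- From 40 to 70: 30/(100 − 40) = +0.5.
- Baseline 100: division by zero, so undefined.

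A 5-point loss near the top thus counts twice as much as a 30-point gain lower down, in the opposite direction. Patients at the maximum drop out, which sits badly with the planned intention-to-treat analysis.

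**Step 3: does the ceiling stay?** Simulation, all inputs assumed: 0–100 score in steps of 5, SD 20, r = 0.7, true effect 10 points, 60 versus 30 patients, 4,000 runs per setting.

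| | Low ceiling | High ceiling |
|---|---|---|
| At maximum at baseline | 1% | 27% |
| At maximum at follow-up | 10% | 67% |
| Observed difference in follow-up means (points) | 9.4 | 4.1 |
| Power, raw change | 0.77 | 0.27 |
| Power, change/maximum | 0.77 | 0.27 |
| Power, change/(maximum − baseline), where defined | 0.78 | 0.56 |
| Power, baseline-adjusted | 0.85 | 0.62 |

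Every method loses power as the ceiling rises, including the adjusted one. With no true effect, the type I error of the adjusted analysis was 0.046–0.048.

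**Step 4: precision of change versus adjusted analysis.** Assume equal SD σ at both times, correlation r and no ceiling. With k = 1/60 + 1/30 = 0.05:

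- variance of the difference in change = 2(1 − r)σ²k;
- variance of the baseline-adjusted difference = (1 − r²)σ²k;
- ratio = (1 − r²)/[2(1 − r)] = (1 + r)/2.

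For an assumed effect of 0.5σ and two-sided alpha 0.05 (also assumed), power ≈ Φ(0.5/√(0.05 × factor) − 1.96), where factor is 2(1 − r) or 1 − r². Here 0.5/√0.05 = 2.236.

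| r | Factor, change | Factor, adjusted | Ratio | Power, change | Power, adjusted | Patients needed with change scores to match 90 adjusted |
|---|---|---|---|---|---|---|
| 0.5 | 1.0 | 0.75 | 0.75 | 0.61 | 0.73 | 90/0.75 = 120 |
| 0.7 | 0.6 | 0.51 | 0.85 | 0.82 | 0.88 | 90/0.85 ≈ 106 |
| 0.9 | 0.2 | 0.19 | 0.95 | 0.999 | 0.999 | 90/0.95 ≈ 95 |

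The gain is about 12, 6 and 0 points. The degree of freedom spent on baseline costs at most about 0.5 points. For an assumed effect of 0.4σ, power goes from 0.43 to 0.54 at r = 0.5 and from 0.64 to 0.71 at r = 0.7.

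**The case against.** Several stronger readings are tempting, and the documents do not support them.

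- *The plan ignores baseline and compares raw follow-up means.* The sentence on group means is introductory. Barthel and the other scales are analysed as change, so the relevant gain is over change scores.
- *Chance baseline imbalance goes uncorrected.* A change score does subtract baseline. It over-corrects when there is regression to the mean, so the fair criticism is lower precision and bias conditional on an observed imbalance.
- *The plan omits covariates.* An analysis plan that is not shown may add them, and a journal article need not list them. Their absence is not the point. The point is the comparison of change that the article states.
- *Large power losses are established.* With an assumed Barthel mean of 65, SD 20, mean gain 12, a cap at 100 and r = 0.7, simulated power rises from 0.50 to 0.63 for 8 points and from 0.68 to 0.83 for 10 points. Without the cap and rounding, the rises are only 0.63 to 0.69 and 0.82 to 0.86. The larger gains depend on a ceiling whose size the documents do not give.
- *Baseline adjustment cures the ceiling.* It does not: adjusted power fell from 0.85 to 0.62 in the simulation above.
- *This re-specifies the primary outcome.* The section Primary outcome measures declares a five-domain compound. Its readmission, cost and home-use parts have no baseline score, so the model does not apply to them.

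In fairness to the plan, the remaining-room index loses less power under a high ceiling than raw change does (0.56 against 0.27), and division by the maximum usefully puts scales on a common range for description. Neither makes the printed claim true.

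**Conclusion.** The ceiling statement is wrong as written. That follows from algebra alone, and the alternative reading of the index does not rescue it. How much a ceiling would matter here is unknown, because the documents give no score distribution. Mild impairment at entry makes one plausible, no more.

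The comparison of change in Barthel and the other disability and impairment scales can be made more precise at almost no cost. The variance reduction is 25% to 5% for r from 0.5 to 0.9, given equal SDs and no ceiling. The power gain is an assumed range, from about 12 points to almost none for a 0.5 SD effect. Confidence is high for the false claim and for the direction of the precision gain, but not for any single power figure.

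Letting a look at normality choose the test is a lesser, related weakness: it allows the reported quantity to switch between means and medians after the data are seen. Its effect on error rates was not quantified here.

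**What to change.** 1. Delete the clause that claims ceiling effects are avoided. State the normalised improvement by formula and keep it as a descriptive summary.
2. For Barthel and the other scales with a baseline score, make the main between-group comparison a prespecified linear model of follow-up score on arm, baseline score, hospital, age, time since stroke and severity. Use robust or bootstrap intervals, and do not let a normality test choose the method.
3. Add a sensitivity analysis suited to bounded scores (proportional-odds or Tobit), because step 2 does not remove the ceiling.
4. Say explicitly that this model does not cover the readmission, cost and home-use parts of the compound outcome.

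Cost: wording, a little more analysis work and a few degrees of freedom. With single terms for baseline, age, time since stroke and severity and two for hospital, that is 6, leaving 90 − 2 − 6 = 82. No new data are needed, since baseline scores and the minimisation factors are already collected.

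### The switch to non-parametric tests and medians for non-normal data has no stated exemption for costs and hospital days, where the question is about mean cost

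*Protocol article*

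**What the plan says.** The Statistical method section of the protocol article opens with its general approach: "We will perform mainly between-subject analysis by comparing the mean outcomes of the experimental group with the mean outcomes of the control group". After a sentence on normalised improvement for the disability and impairment scales, it gives a rule for choosing the test: "Depending on whether the data is following a normal distribution, we will use parametric or non-parametric statistics". The summary measure follows: "In the case of non-normal data, medians will be reported". No outcome is named as an exception.

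The same section then takes up the Table 3 variables. Under Readmission: "We also compare the days of hospitalization and their associated costs", with vascular risk markers to be used as covariates. For the cost domain the plan reads: "We compare the total cost of rehabilitation therapy/hour provided at the hospital or in the community and transportation costs/hour between the hospital and home". The time points are months 3 and 12. The conclusion to be drawn is stated: "These outcomes allow us to evaluate the RGS’s effectiveness to reduce the cost of treatment". No other test or summary measure is given for these variables.

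Therapy cost also feeds the primary compound score, whose third domain is "cost of treatment (total cost of the therapy" (Primary outcome measures). The Study rationale expects costs to fall, and the Discussion expects lower costs for hospitals and families.

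**The concern.** A payer's question about cost is a question about the total, which is the arithmetic mean times the number of patients. The section names means as its target, but its own rule replaces them once data fail a normality check. Readmission days and costs are likely to be zero for most patients, and therapy cost is typically right-skewed, so these are the variables most likely to be switched.

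Two things follow. The reported medians cannot be multiplied up to a budget. The usual two-group rank test asks whether patients in one arm tend to have larger values than patients in the other, and the answer can be yes when mean costs are equal. The test is then not in error on its own terms. The error lies in reading its result as a saving or an excess. A difference in shape is plausible here, because RGS brings equipment and support for every user while the predicted savings lie in fewer readmissions and hospital stays.

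**Working it through.** **Sample size.** Allocation and blinding gives three hospitals, each with 20 intervention and 10 control patients: 3 × (20 + 10) = 90, that is 60 v 30. The size rests on feasibility, so there is no power figure to reproduce.

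**Medians, without simulation.**
- Readmission days: if a share p of an arm is readmitted and p < 0.5, the median is 0 whatever was spent. Shares of 10%, 20% and 40% all give a median of 0.
- Skewed cost: a lognormal with mean m and log-SD s has median m × exp(−s²/2). With m = 1000, s = 0.6 gives 835 and s = 1.0 gives 607. The means are equal and the medians differ by 228.

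**Rank test, without simulation.** Assume RGS 10% readmitted for a mean of 20 days and control 20% for a mean of 10 days. Both means are 0.10 × 20 = 0.20 × 10 = 2.0 days. For a random pair of patients:
- RGS readmitted, control not: 0.10 × 0.80 = 0.08
- control readmitted, RGS not: 0.90 × 0.20 = 0.18
- both readmitted: 0.10 × 0.20 = 0.02

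The RGS patient has more days with probability at most 0.08 + 0.02 = 0.10, and the control patient with probability at least 0.18. The rank test therefore leans towards fewer days on RGS although mean days are equal.

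**Simulation.** Arms of 60 and 30, equal true means, 20,000 trials per row. These points are assumptions, not in the article: two-sided alpha 0.05, Mann-Whitney as the rank test, lognormal costs, zero-inflated hospital days, and Shapiro-Wilk in each arm as the normality check. The check was run on 3,000 trials per row and sent at least 99.9% of them to the non-parametric branch.

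| Scenario (RGS v control) | Mann-Whitney | Welch | Main direction of Mann-Whitney signals |
|---|---|---|---|
| Cost, log-SD 1.0 v 1.0 | 5.1% | 5.4% | none |
| Cost, log-SD 0.8 v 1.0 | 14.7% | 6.8% | RGS dearer |
| Cost, log-SD 0.6 v 1.0 | 39.6% | 9.1% | RGS dearer |
| Cost, log-SD 1.0 v 0.6 | 37.7% | 5.0% | RGS cheaper |
| Cost, log-SD 0.5 v 1.2 | 75.9% | 13.6% | RGS dearer |
| Days, 20% × 10 v 20% × 10 | 4.8% | 5.8% | none |
| Days, 10% × 20 v 20% × 10 | 23.2% | 4.1% | fewer on RGS |
| Days, 10% × 20 v 40% × 5 | 84.1% | 7.0% | fewer on RGS |

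**Milder cases, also with equal means.**
- An added RGS cost exactly offset by fewer readmissions: 5.9% (250 added, 15% v 20% readmitted), 8.0% (500 added, 10% v 20%) and 11.7% (750 added, 5% v 20%). Welch gave 5.4%, 5.8% and 6.5%.
- Therapy cost alone, with a fixed RGS cost making up 10% to 30% of the total: about 5% to 11% at log-SD 0.4 to 0.5. With a 30% share it was about 21% at log-SD 0.8 and about 30% at log-SD 1.0.

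**Covariates.** Readmission days and costs are to be analysed with vascular risk markers as covariates. A simple two-group rank test has no place for them, so the switch and the covariate sentence cannot both be followed in that form.

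**The case against.** The best defence is that the article commits to less than the simulations suppose.
- It names no rank test. A bootstrap or permutation comparison of means is also non-parametric.
- The Abstract promises a health economic analysis and the full protocol is available on request, so cost methods may be settled there.
- The rule follows a sentence about disability and impairment scales, and the Table 3 variables are introduced separately, so a narrower scope can be argued.
- The covariate sentence points to a model for readmission days and costs, which is where some of the largest rates arise.

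Much of this stands as a limit on size. A reader might infer that the plan is bound to Mann-Whitney and will therefore report false savings in a quarter or more of trials. The documents do not support that, because the test is not named and the large rates need strong differences in shape. A reader might also infer that readmission costs belong to the primary cost domain. They do not: that domain is therapy cost, readmission is a separate domain measured by the count of patients readmitted, and the sum of therapy and readmission cost in the offset scenarios is not a stated endpoint. Nor would a median of 0 hide a change in how many patients are readmitted, since that number is already compared.

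The core is untouched. The rule speaks of the data in general, beside intention-to-treat and missing-data rules that are also general. The reporting of medians is explicit, and it conflicts with a target stated as means.

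**Conclusion.** The point holds as a conflict between the stated target and the stated rule. As written, skewed costs and hospital days would be summarised by medians, which cannot show whether spending fell, and under the usual choice would be tested by ranks, which do not test equal means. The covariate plan for readmission days and costs adds a second conflict.

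The size depends on assumptions. With equal shapes there is no excess over about 5%. With equal means and different shapes, the rank test signals a saving or an excess in about 6% to 12% of trials in mild cases and 20% to 40% or more in strong ones, in either direction. Welch gave about 3% to 9% across the runs and 14% in one extreme case, so comparing means is not exact at 30 controls, but it addresses the right quantity. Reading the target as mean cost rests on the opening sentence of the section and on the cost-reduction aims, since the article never uses the term mean cost. The matter is clearest for cost of treatment, which has no covariates and is a primary domain. It deserves correction but does not touch the clinical comparisons.

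**What to change.** Add a sentence to the Statistical method section exempting costs, hospital days, therapy hours and travel from the normality switch. Compare arithmetic means between the arms and report the mean difference with a bootstrap 95% confidence interval. Alternatively, take it from a generalised linear model: for example gamma with log link for positive costs, and a two-part or similar model where zeros are common. For readmission days and costs, include the planned risk-marker covariates. Give medians as description only. The comparison of the number readmitted needs no change.

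The cost is a sentence of text and a few lines of code, with no new data. The bootstrap and the models were not simulated here; Welch stood in for them. The drawback is wide intervals at 90 patients. In one illustrative scenario, with therapy and readmission cost summed and true means of 3249 v 4245, Welch detected the saving in 24.3% of trials. The rank test did so in 24.7%, so comparing means lost almost nothing there.
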